## Abstract

**Background:**

Mental health literacy is a promising avenue of intervention for addressing the development of psychopathology, as well as its associated consequences, such as a decrease in academic performance. The current study aims to test the effectiveness of such an intervention in high school students, focusing on two main formats of delivery: (1) automated and (2) blended.

**Methods:**

To achieve this aim, a randomized clinical trial with direct comparisons at three time points between three conditions (automated, blended, and waitlist) was designed. Power analyses yielded a necessary sample size of 264 high school students. The participants will be selected from Romanian high schools.

**Discussion:**

The current study aims to contribute to the mental health literacy literature by testing the effectiveness of an educational intervention concerning mental health in terms of its benefits for reducing psychopathology and increasing academic performance. The success of such an intervention bears important implications for addressing mental health in the educational system.

**Trial registration:**

Clinicaltrials.gov Identifier: NCT06217744, version 1, 22 January 2024.

**Supplementary Information:**

The online version contains supplementary material available at 10.1186/s13063-024-08270-y.

## Mental health literacy and academic performance

### Background

Mental disorders represent one of the most important risk factors associated with disability, accounting for more than a quarter of the responsible causes for disability in people between the ages of 15 and 44 [1]. The worldwide prevalence of any mental disorder in children and adolescents is estimated at 13.4% [2]. Mental disorders are associated with school absenteeism [3, 4], academic-related stress and poorer academic performance, learning capacity, and physical and mental health outcomes [5].

Even though there are effective mental health interventions for the youth, such as psychotherapy [6], canine-assisted psychotherapy [7], or psychiatric medication [8], to name a few, there are accessibility barriers, ranging from geographical challenges to awareness of such problems in these populations. Some of the main reasons why adolescents avoid seeking mental health help include perceived stigma and shame associated with help-seeking and insufficient mental health-related knowledge [9]. At the same time, a history of pleasant experiences with mental health services and mental health literacy constitutes some of the most important facilitators for seeking professional help [10].

This clinical trial aims to address the aforementioned issues by testing the effectiveness of an intervention meant to increase mental health literacy in adolescents through a curriculum available at school level.

### Framework and rationale of the present study

Mental health literacy refers to having knowledge of how to recognize, deal with and prevent mental disorders [11]. Mental health literacy in adolescents can help develop support from parents, friends, or other members in a community, by doing so greatly complementing mental health services [12].

Unsurprisingly, poorer mental health literacy is associated with increased psychopathology, such as depression [13, 14], anxiety, stress, and other mental health outcomes [14]. There have been efforts to develop mental health literacy interventions, such as The Youth Education and Support (YES) Program, which is geared to grades 5–8 [15]. Although there is a wide range of mental health literacy interventions [16–18], most of them are delivered in a classroom format [19, 20], even though delivery through the Internet could be a viable option [16].

Most of the research in this field has been conducted in Australia, and it is unclear to what extent those findings are generalizable to different cultures and economically diverse countries [16]. The current MHL intervention is informed by "The Mental Health & High School Curriculum Guide" [21], an evidence-based mental health curriculum initially developed in Canada. Our intervention follows the structure of the aforementioned curriculum (details about the content of the intervention can be found in the “Methods” section of this paper). However, it is not a direct translation. Instead, it incorporates cultural adaptations to suit the Romanian context. Adjustments were made to address specific cultural factors in Romania. This includes adapting the language to reflect local stigmatizing words or expressions, addressing prevalent myths about mental disorders, and incorporating examples and role models relevant to Romanian teenagers. The adaptation process involved input from educational and mental health experts, school focus groups, and educational advocacy groups. The development of the intervention took 6 months. This period included extensive literature reviews, thorough documentation, and group discussions among professionals to ensure comprehensive coverage of key mental health issues relevant to teenagers (e.g., disorders usually starting in adolescence, such as eating disorders, or that might be of particular relevance in academic contexts, such as ADHD), appropriate and engaging language, and relevant examples tailored to their age and interests.

### Objectives

The goal of this study is to test the effectiveness of an intervention designed to promote mental health literacy in adolescents, in the format of a randomized clinical trial.

We aim to (1) determine whether this intervention has an impact on mental health, (2) observe if this intervention has an impact on fostering academic performance, particularly in disadvantaged students (i.e., academic resilience), and (3) examine what type of intervention delivery is more effective: automated versus blended format.

## Methods/design

### Trial design

This study is an exploratory randomized clinical trial involving comparisons at three time points (i.e., pre-intervention, post-intervention, 1 month follow-up) between three conditions: (a) automated intervention (consisting of an online, automated delivery of the intervention), (b) blended intervention (online automated delivery of the intervention plus regular contact with facilitators), (c) waitlist, with an allocation ratio of 1:1:1. The contrast between the automated and blended interventions is meant to highlight whether contact with facilitators while receiving psychoeducational materials might have an additive effect.

The design of this study complies with the Consolidated Standards of Reporting Trials (CONSORT) guidelines [22] and follows the Standard Protocol Items: Recommendations for Interventional Trials (SPIRIT) Statement 2013 [23] (see also Additional file 1: SPIRIT checklist and schedule of enrollment, interventions, and assessments).

The current trial is part of a larger project that aims to assess adolescent mental health in Romanian high schools.

### General description of the tested application

SCHOLARS is a web-based mental health literacy intervention containing six modules as follows: Module 1: The Stigma of Mental Illness; Module 2: Understanding Mental Health and Mental Illness; Module 3: Information on Specific Mental Illnesses; Module 4: Experiences of Mental Illness; Module 5: Seeking Help and Finding Support; Module 6: The Importance of Well-being. These modules will have both text and videos through which the users will progress. Both the automated and blended interventions are designed to last for three months, with two modules being delivered per month. Participants are encouraged to go through the materials at their own pace and have the option to revisit previous modules as needed. Participants can access the intervention from any location.

The intervention can be accessed through a LimeSurvey link and is compatible with various devices such as computers, tablets, and mobile phones. To ensure that the intervention will be properly delivered through this medium, we initially conducted a brief pilot test on a convenience sample consisting of university students. No issues were encountered during this phase.

Detailed information about the intervention is available on the project's website, which is linked on the initial page of the intervention. This resource allows participants to learn more about the study team responsible for the development of the intervention as well as the associated written and visual materials. Additionally, participants can ask any specific questions by emailing the research team; the email address is provided in the consent form.

### Study setting

The data will be collected from several high schools in Romania. They will be both state operated and privately owned. High schools will be enrolled based on their availability and willingness to participate in the study.

### Inclusion and exclusion criteria

The current trial will include Romanian high school students, specifically those in grades 9 through 12, aged 14 to 18 years old. Participation in the trial is open to all students within this age and grade range who have access to the internet, regardless of their Internet source. It does not matter where the Internet access comes from, be it from a home connection, school-provided resources, public libraries, or other means. The primary requirement is that these students can reliably access the Internet to participate in the study, ensuring that all eligible participants can engage. Of note is that, in 2021, Romania was ranked on the 5th place in the world in terms of Internet speed and, according to Eurostat, boasts one of the highest Internet penetration rates in Europe [24]; therefore, access to the Internet of our target population is not problematic.

### Study conditions

#### Experimental—automated intervention

This intervention will last for 3 months, with two psychoeducational modules delivered per month. The participants will receive a total of 6 modules, which will include both text and video-delivered information, as well as quizzes and practical activities.

#### Experimental—blended intervention

This intervention will last for 3 months, with two psychoeducational modules delivered per month. The participants will receive a total of 6 modules, which will include the same content as in the educational intervention. In addition, the participants will also have the possibility to engage with a facilitator on a regular basis, either via online live sessions (e.g., via Skype) or on a forum where they can ask questions and receive replies from the team.

### Sample size

R version 4.2.2 for Windows (R Foundation for Statistical Computing, Vienna, Austria) was used for the sample size calculation in a linear mixed-effect model (sjstats package). The R statistical computing environment will also be used for future model fitting and evaluation.

We used appropriate methods for two-level-designs [25] to determine sample size requirements for a cRCT with 3 experimental groups, 4 classrooms per experimental condition, 22 participants per cluster. For our linear mixed-effects model, a sample size of approximately 88 participants per experimental condition for a total sample size of 264 was sufficient to achieve 80% power to detect an effect size of Cohen’s *d* = 0.4 at an alpha level of 0.05. A medium effect size was assumed based on previous work on digital mental health literacy interventions [26].

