#### Statistical methods

Our study will consist of a multisite cluster randomized trial in which the unit of measurement is at student-level, while randomization takes place at the unit of assignment, at classroom-level. Consequently, it is a low bias cluster-level RCT with potential joiners (i.e., individuals not in intervention clusters at random assignment but who enter later) being excluded and scant possibility of “contamination” or “treatment spillover” to the control classrooms. Analyses will employ linear mixed model with individual-level repeated measures nested within classrooms, nested within schools. Adhering to WWC group design standards [42], the model will include indicators for each intervention period and interaction terms for assignment to the intervention group and the period associated with the intervention. We will also report on robust standard errors from our fitted models to adequately account for dependence within clusters.

Nevertheless, youth research, and especially youth mental health research, has unique challenges concerning data gathering. First, although we adhere to a strategic research design to reduce missing data, patterns of attrition relating to individual and cluster-level factors will be investigated, including links to social and health variables. Second, challenges in gathering parental consent after classroom-level assignment to experimental condition would yield higher number of leavers, which constitutes individual-level attrition [42]. If data is missing at random, our analytic choice will yield unbiased estimates of treatment effects [43]. If data is missing not at random, weighting and multiple imputation would be used. In line with WWC standards [42] for cluster-level assignment RCTs, we will employ regression imputation, maximum likelihood, or nonresponse weights to address missing values while providing evidence that the approach appropriately adjusts the standard errors for clustering.

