## Discussion

The current trial aims to test the effectiveness of a mental health literacy intervention for high school students, aimed at improving academic performance, as well as increasing well-being and decreasing symptomatology. The intervention will be delivered via two different formats: (1) an educational one, which will be fully automated, and (2) a blended one which will additionally allow contact with facilitators, and it will be contrasted against a waitlist condition. Testing mental health literacy interventions is paramount, as not much is known about their effectiveness on outcomes such as academic performance and symptomatology. Furthermore, since the goal of mental health literacy interventions is to fill in the gaps that other mental health interventions cannot, in terms of their reach and cost-effectiveness, it also becomes highly relevant to test various modes of implementing such interventions, including fully automated ones. Additionally, testing the effectiveness of such interventions in varied cultural and socioeconomic contexts is timely, as this has been previously recognized as a limitation of the literature [19].

This endeavor, however, is not without its caveats. Firstly, contrasting active interventions against a waitlist control group can artificially inflate effect sizes. However, this approach is more ecological and cost-effective. If results will favor the SCHOLARS intervention, future studies should contrast it against active control conditions or psychological placebos. Secondly, there may be limited adherence to the intervention by the participants (i.e., dropouts). To this end, we aim to monitor and maintain close and constant contact with the enrolled schools, as to minimize drop-out and the risk of non-adherence by participants.

To conclude, the current study has the potential of advancing the field of mental health literacy interventions for adolescents. The success of such interventions might represent an important avenue for preventively addressing the development of mental health concerns and their associated consequences such as decreased academic performance.

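### The stated 80% power for d = 0.4 with 88 students per arm cannot be reproduced from the inputs given; it needs an unstated contrast, sidedness, ICC or baseline correlation

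*Protocol article*

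**What the plan says.** The Sample size section describes the calculation as follows: "We used appropriate methods for two-level-designs [25] to determine sample size requirements for a cRCT". The layout is "3 experimental groups, 4 classrooms per experimental condition, 22 participants per cluster", the assumed effect is Cohen's d = 0.4 and alpha is 0.05. It concludes that "a sample size of approximately 88 participants per experimental condition for a total sample size of 264 was sufficient to achieve 80% power". The Abstract turns this into a requirement: "Power analyses yielded a necessary sample size of 264 high school students".

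Three other places bear on the figure:

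- Trial design sets three arms "with an allocation ratio of 1:1:1", and Objectives makes automated versus blended one of the three aims.
- Statistical methods puts randomisation at classroom level and gives the model: "Analyses will employ linear mixed model with individual-level repeated measures nested within classrooms, nested within schools". It includes assignment-by-period interaction terms.
- Statistical methods foresees leavers when parental consent is sought after assignment, and the Discussion foresees dropouts.

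The Sample size section gives no ICC, design effect, sidedness, contrast, correlation between repeated measurements or allowance for loss.

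**The concern.** The printed inputs are complete enough to test the claim in its most favourable simple form: one pairwise contrast, two-sided, with no clustering. It falls short there. Classroom clustering, which is the reason for using two-level methods, can only lower power for a single-time-point comparison. Something not printed must therefore be carrying the calculation, and a reader cannot tell what.

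The stake is how results are read. If 80% power for 0.4 SD is taken at face value, a null result will be read as evidence against an effect of that size. This applies equally to automated versus blended, which rests on the same 88 against 88.

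**Working it through.** **Inputs from the protocol article (Sample size, Trial design).** d = 0.4 with SD = 1; alpha 0.05; m = 22 students per classroom; k = 4 classrooms per arm; three arms. Sidedness is not stated, so two-sided is assumed first.

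**1. Headcount.** 4 × 22 = 88 per arm and 3 × 88 = 264. These agree with the text.

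**2. The stated 80%, ignoring clustering.** SE = √(2/88) = 0.151 and 0.4/0.151 = 2.65. Power is 75.6% by the normal approximation and 75.1% by the two-sample t-test. Solving for 80% gives 99 per arm (normal) or 99.08, rounded up to 100 (t-test), so 297 to 300 in total. The figure is not reproduced.

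**3. With clustering, no gain from repeated measures.** DEFF = 1 + (22 − 1) × ICC; SE = √(2 × DEFF/88). Power is given by the normal approximation and by the noncentral t with 12 − 3 = 9 degrees of freedom. The ICCs are assumptions; the article gives none.

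| ICC (assumed) | DEFF | Effective n per arm | Power, normal | Power, 9 df |
|---|---|---|---|---|
| 0 | 1.00 | 88.0 | 76% | 66% |
| 0.01 | 1.21 | 72.7 | 67% | 58% |
| 0.02 | 1.42 | 62.0 | 61% | 51% |
| 0.05 | 2.05 | 42.9 | 46% | 38% |
| 0.10 | 3.10 | 28.4 | 33% | 27% |

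**4. Choices that could bring the figure to 80%.** None is stated in the Sample size section.

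- *Baseline adjustment.* The variance is multiplied by 1 − r², where r is the baseline correlation of classroom means: r = (m × ICC × CAC + (1 − ICC) × IAC)/DEFF. CAC and IAC are the classroom-level and individual-level correlations over time, assumed here as 0.8 and 0.7.

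| ICC (assumed) | r | DEFF × (1 − r²) | Power, normal | Power, 9 df |
|---|---|---|---|---|
| 0.01 | 0.72 | 0.59 | 93% | 87% |
| 0.02 | 0.73 | 0.66 | 90% | 83% |
| 0.05 | 0.75 | 0.89 | 81% | 71% |

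  Conversely, the r needed for 80% (normal / 9 df) is 0.61 / 0.71 at ICC 0.02, 0.75 / 0.81 at 0.05 and 0.84 / 0.88 at 0.10.
- *One-sided test (normal).* 84% at ICC 0 and 78% at ICC 0.01.
- *Both active arms pooled against waitlist (176 vs 88, normal).* 87% at ICC 0, 79.5% at 0.01 and 57% at 0.05. This says nothing about automated versus blended.
- *Three-arm F-test, no clustering.* 78% if one arm differs from the other two by 0.4; 83% at f = 0.2.
- *A two-arm total inflated to 264.* 198 × (1 + 21 × 0.016) ≈ 264, but this treats all 264 students as two arms.

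**5. Loss.** The 264 is both the planned number and the number on which 80% is claimed, so the stated figures leave no margin. As an illustration, an assumed 20% loss leaves 17.6 per classroom. At ICC 0.05, DEFF = 1 + 16.6 × 0.05 = 1.83 and the unadjusted power in step 3 falls from 46% / 38% to 42% / 35%.

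**The case against.** The best reply is that steps 2 and 3 test an analysis the trial does not plan. Power is claimed for the authors' linear mixed-effects model, which Statistical methods describes as repeated-measures with assignment-by-period interactions. In such a contrast stable classroom differences cancel, and only classroom-by-period variation inflates the variance. With stable classroom effects alone, the variance factor for change is 2(1 − r), and r of about 0.55 gives 80% (normal). The degrees of freedom also depend on the random-effects structure, which may sit in a fuller plan. The contrast is open too: the first objective can be read as active arms against waitlist. Finally, the article is a condensed account of a trial that calls itself exploratory.

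Much of this stands. A reader might infer from the 38% to 46% at ICC 0.05 that the trial does not have 80% power. The documents do not support that: ICC 0.05 is an assumption, and the planned model may gain enough from baseline. Nor is it an error to use a two-level calculation before a three-level analysis, or to take d = 0.4 from related work.

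The reply does not rescue the printed sentence. It works only by adding a correlation, an ICC, a sidedness or a pooled contrast that the section does not give. The exploratory label does not alter what the power statement asserts.

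**Conclusion.** The point holds in limited form: the 80% does not follow from the inputs stated beside it. For a two-sided pairwise contrast without a repeated-measures gain, power is at most about 75%. For assumed ICCs of 0.01 to 0.10 it is about 67% down to 33% (normal), or 58% down to 27% (9 df). The shortfall at ICC 0 uses only the article's figures plus a two-sided test; the rest depends on assumed ICCs.

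Actual power under the planned model cannot be determined from the article. With baseline correlation near 0.7 to 0.75 it reaches 80% at an ICC of 0.02 or below on either reference distribution. At 0.05 it does so only by the normal approximation. The claim is unsupported rather than disproved, and the Abstract's description of 264 as the required number is unsupported with it.

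**What to change.** Recalculate for the planned mixed model. Replace the 80% statement in Sample size, and the matching Abstract line, with the power or detectable effect that 12 classrooms of 22 give. The new paragraph should:

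- name each contrast (each active arm against waitlist, automated against blended, and the pooled contrast if intended) and the sidedness;
- state the ICC and the baseline or repeated-measures correlation actually used, and show results over a range of both;
- state the expected loss and the classroom-level degrees of freedom.

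The authors should use their own inputs and mark any others as assumptions. The ICCs and correlations used in this check are illustrations and should not be adopted as design values.

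The cost is one rewritten paragraph, one Abstract line and probably a less favourable stated figure. Enrolment need not change.

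### The only sample size given, 264, carries no allowance for loss although the protocol foresees leavers and dropouts, so the stated 80% power is somewhat too favourable if about 264 students are enrolled

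*Protocol article*

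**What the plan says.** The Sample size section sets out a cluster design with "3 experimental groups, 4 classrooms per experimental condition, 22 participants per cluster" and concludes that "a sample size of approximately 88 participants per experimental condition for a total sample size of 264 was sufficient to achieve 80% power", for a Cohen's d of "0.4 at an alpha level of 0.05". The Trial design section adds that the three conditions are compared "with an allocation ratio of 1:1:1". The Abstract repeats the figure: "Power analyses yielded a necessary sample size of 264 high school students". No other enrolment target, expected loss rate or inflation factor appears in the article.

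Two other sections foresee loss. Statistical methods says that "challenges in gathering parental consent after classroom-level assignment to experimental condition would yield higher number of leavers", classes this as individual-level attrition, and plans attrition analyses with imputation, maximum likelihood or weighting. It also excludes students who join a classroom after randomisation. The Discussion lists as a caveat that "there may be limited adherence to the intervention by the participants (i.e., dropouts"), and offers close contact with schools as mitigation.

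**The concern.** The power statement belongs to a design with 22 students contributing in each of 12 classrooms. The same article gives two routes by which fewer may contribute, and it rules out late joiners as replacements. The planned missing-data methods deal with bias and standard errors; they do not restore lost information.

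If enrolment stops at about 264, the quoted power and the detectable effect of 0.4 describe a larger data set than the one to be analysed. Readers of a null result could then give it more weight than the design supports.

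**Working it through.** **Inputs from the article.** 3 arms, 4 classrooms per arm, 22 students per classroom, d = 0.4, alpha 0.05, power 80% (Sample size). The article does not give the ICC, the correlation between repeated measures, the sidedness, the contrast tested or a loss rate.

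**Step 1: the total.** 4 × 22 = 88 per arm and 3 × 88 = 264. The stated total is the design count exactly, so no loss factor is contained in it.

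**Step 2: the stated power.** The 80% cannot be uniquely reproduced from what is given. A plain two-sided comparison of two arms at ICC 0 has power Φ(0.4/√(2/88) − 1.960) = Φ(2.653 − 1.960) = 75.6%, and 80% would need 99 per arm. A one-sided test gives 84.3%. A three-group F test with one arm 0.4 SD from the other two gives 78.4%. None of these involves a loss factor. For the next step the stated 80% is taken as correct for complete data.

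**Step 3: the effect of loss.** Assumptions: a fraction L of students is lost evenly over classrooms, lost students contribute nothing, and the test is two-sided. With m = 22(1 − L), the variance of the contrast rises by

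ratio = {[1 + (m − 1)ICC]/m} / {[1 + 21 ICC]/22}.

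Power = Φ(2.802/√ratio − 1.960), where 2.802 = 1.960 + 0.842. The effect detectable with 80% power = 0.4 × √ratio.

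Each cell shows ratio; power; detectable effect.

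| Assumed loss | Remaining of 264 | ICC 0 | ICC 0.02 | ICC 0.05 |
|---|---|---|---|---|
| 10% | 238 | 1.11; 75.7%; 0.42 | 1.08; 77.0%; 0.42 | 1.05; 78.0%; 0.41 |
| 20% | 211 | 1.25; 70.7%; 0.45 | 1.17; 73.5%; 0.43 | 1.12; 75.6%; 0.42 |
| 30% | 185 | 1.43; 65.0%; 0.48 | 1.30; 69.2%; 0.46 | 1.20; 72.5%; 0.44 |

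Worked example at 20% loss and ICC 0.05: m = 17.6; ratio = (1.83/17.6)/(2.05/22) = 0.1040/0.0932 = 1.116; power = Φ(2.802/1.056 − 1.960) = Φ(0.69) = 75.6%.

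Power falls less at a higher ICC because the 80% starting point is held fixed and losing students within a classroom then matters less. It does not mean that a high ICC is harmless.

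**The case against.** **No contradiction in the text.** Nothing in the article says that 264 is the number enrolled. Sufficient and necessary both read naturally as the number the calculation requires; the Recruitment section sets no target, and randomisation is not capped. A reader might infer that the protocol makes 264 both the enrolled and the analysed number and so contradicts itself. The text does not support that, and this part of the objection stands. What remains is conditional: one figure is given, without loss, and the article does not say what it counts.

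**The foreseen loss is softer than it looks.** Students without parental consent may never be among the 22 counted per classroom, since the Auditing section has consent checked. The Discussion speaks of a possibility and of adherence, and a student who stops the modules can still supply outcomes. This stands as a limit on the size of the loss. It does not remove it: the article itself classes leavers as attrition and equates limited adherence with dropouts.

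**Partial data help.** The mixed model covers three time points, so a student with some follow-up still contributes. This softens the figures above but does not cancel the loss.

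**The 80% holds only with no loss at all.** A reader might infer this too, and it is too strong. The article says approximately 88, and modest loss costs only a few points. Nor is full retention known to be sufficient: the plain pairwise test reaches only 75.6% at ICC 0. With no gain from repeated measures, the design effects of 1.42 and 2.05 would give about 60% at ICC 0.02 and 46% at ICC 0.05 before any loss. The table therefore rests on a starting point that cannot be checked, and its ranges should not be written into the protocol as fact.

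**Exploratory trial, condensed article.** The Trial design section calls the trial exploratory, and an article may leave detail to a fuller document. But the article makes a formal power claim, and a stated claim should fit the expectations stated beside it.

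**Conclusion.** The point holds in a limited form. The 264 is exactly the design count and contains no allowance for loss, while the article foresees leavers and dropouts and excludes joiners. If about 264 students are enrolled, the information at post-intervention will fall short of what the 80% at d = 0.4 refers to.

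The shortfall is moderate. On the assumptions in the working, 10% loss costs about 2 to 4 percentage points and 20% loss about 4 to 9, with the detectable effect rising to 0.41–0.42 and 0.42–0.45. Partly observed students would reduce these losses somewhat. The loss rates and ICCs are illustrative, and the 80% itself is taken on trust.

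**What to change.** In the Sample size section and the Abstract, say that 264 is the number of students with analysable post-intervention data that the calculation requires. Then restate the power, or the effect detectable with 80% power, for the number expected to remain out of those enrolled. Use the investigators' own expected loss, and the ICC and repeated-measures correlation from their calculation, and state these values.

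The cost is a few sentences and a slightly less favourable power or detectable effect. No extra classrooms or students are required.
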